### Other measures

#### Socioeconomic and demographic variables

Socioeconomic and demographic characteristics of participants will be assessed by online questionnaire and include household composition, incomes and how they perceive their financial situation, age, gender and education level of each household member.

#### Away-from-home consumption

Away-from-home consumption of each household member will also be estimated, since a high away-from-home food consumption can impair the ability of the food supply to provide an accurate estimation of dietary quality and nutrient intakes [45]. To this end, participants will be asked by questionnaire how often they generally eat away from home (four categories possible: company restaurant/canteen, restaurant and catering, fast-food, meal with friends, with six possible answers (“every day”, “4–6 times/wk”, “1–3 times/wk”, “1–3 times/month”, “< 1 time/month”, “never or rarely”). Household members will be also asked whether they tend to consume F&V, meat, fish and dairy products mostly at home, away-from-home, both in and outside the home, or never.

#### Gardening experience

Gardening experience prior to the project will be assessed by an online questionnaire asking participants about their experiences and perceived competence in gardening.

### Planned statistical analysis

Summary statistics (mean, median, standard deviation and frequency distribution) will be generated for baseline characteristics. Baseline characteristics will be compared between the experiment and control groups using one-way ANOVA or a Kruskal-Wallis test for continuous variables, and chi-square or Fisher’s exact tests, for categorical variables. The magnitude of change within and between groups between *t*_0_ and *t*_1_ will be calculated.

Data will be analysed to address the research questions, applying appropriate linear mixed models. Differences within and between groups in the outcome parameters will be analysed. Time, group and their interaction will be defined as fixed factors. Subject and group will be included as random factors. If imbalances occur between groups, the baseline values will be treated as covariates.

All analyses will be performed with the SAS statistical software package Ver. 9.4 for Windows (SAS Institute, Cary, NC, USA), with statistical significance at *p* < 0.05.

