## Methods/design

### Study setting, population and design

The JArDinS study is part of the ongoing SURFOOD-Foodscapes project evaluating the effects of urban foodscape on food styles in the Montpellier Metropole (France). The project is divided into 6 different work packages, the main one consisting of a quantitative survey on food purchase behaviors (Mont’panier survey). The JArDinS study is the work package addressing the impact of urban gardening on sustainable lifestyles.

JArDinS is a pretest-posttest quasi-experimental research project (Fig. 2). The design comprises a natural experiment group of new gardeners starting gardening in a community garden in Montpellier and a control group of participants from a survey on food behaviors undertaken as part of the SURFOOD-Foodscapes project. Participants will be surveyed at enrolment and 12 months later. Quasi-experimental design was chosen rather than a randomized, controlled experiment since random sampling is impossible in French community gardens, where new membership and plot renewal in community gardens are decided by local authorities or private managers.

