Data collected from new gardeners will be compared with those from a group of residents who have never participated in a community garden. This control group will be selected using frequency matching from a subsample of persons who participate in a survey on food behaviors undertaken as part of the SURFOOD-Foodscapes project (“Mont’Panier” survey), and who have no experience in community or home gardening. This survey is being conducted in 500 households of Montpellier from May to December 2018 using quota sampling based on age and household composition. Frequency matching involves the selection of an entire stratum of reference subjects (control group) with matching-factor values equal to that of a stratum of index subjects (natural experiment group) [29]. The control group will be matched for age range, gender, household income and household composition, and live as close as possible to the new gardeners.

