The study has some limitations. First, although several well-known confounders will be measured in the study and controlled in the analyses, the use of a natural experiment makes it difficult to control all extraneous variables, and so unknown and unmeasured extraneous variables may affect the results, threatening validity. Second, the natural experiment and control groups might differ in some pre-study characteristics because participants are not assigned randomly to the two groups, which is liable to bias the estimates of the experiment. Non-random design can threaten the internal validity of the study, which is critical for determining a causal relationship [25]. To ensure similarity between groups, the members of the control group will be selected using pairwise matching on sociodemographic characteristics known to be associated with the outcomes of interest. Third, we will collect frequency and type of foods consumed away from home, but this information lacks precision regarding the quantity consumed and the price paid for food out of home. Nonetheless, studies have shown that nutrients derived from foods purchased at supermarkets provide a good estimate of dietary intake [51–53]. In addition, in France, most meals are still consumed at home [54] and so we expect food supply to be a good proxy of food intake. Fourth, the economic dimension of sustainability will be assessed only by the cost of the diet: other aspects such as ethical consideration (e.g., economic fairness including fair remuneration for producers) [55] will not be investigated.

Public policies are now emerging in France to promote good health and sustainable development of cities. For instance, community gardening undertaken jointly with other food initiatives (at local and national levels) such as Community Supported Agriculture, or projects at canteens could favour access for all to healthy, good quality local products and thus contribute to more sustainable food systems. The JArDinS study based on a natural experiment will yield findings to guide public and private policies for the organization, physical planning and assignment of urban areas. If the study finds evidence for potential benefits of community gardens to attract individuals to more sustainable lifestyles, then access to a community garden, as way to help promote health and wellness, needs to be facilitated.

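### The conditional baseline-covariate rule, read plainly, does not adjust the time-by-group effect, and it conflicts with the promise that confounders are controlled

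*Protocol article*

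**What the plan says.** The study has two visits: "Participants will be surveyed at enrolment and 12 months later". The Planned statistical analysis section of the protocol article proposes linear mixed models in which "Time, group and their interaction will be defined as fixed factors" and "Subject and group will be included as random factors". It plans baseline comparisons ("Baseline characteristics will be compared between the experiment and control groups using one-way ANOVA or a Kruskal-Wallis test for continuous variables") and then gives its only rule for covariates: "If imbalances occur between groups, the baseline values will be treated as covariates".

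The limitations paragraph of the Discussion is unconditional: "although several well-known confounders will be measured in the study and controlled in the analyses".

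The two accounts of the matching differ. Under Study setting, population and design: "This control group will be selected using frequency matching from a subsample of persons". In the Discussion: "the members of the control group will be selected using pairwise matching on sociodemographic characteristics". The analysis section refers to neither.

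**The concern.** The groups are not randomised, so control of confounding decides whether the result can be read causally, and the abstract claims a design that allows this. The plan states one analytic remedy. Three things about it look wrong.

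- It enters baseline values into a model whose response already contains baseline, without saying that they interact with time. Such a term may not reach the effect of interest at all.
- If the baseline value is the outcome at baseline, the same number stands on both sides of the model.
- Adjustment waits for an observed imbalance, although a variable can confound whether or not a baseline comparison picks it up.

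At stake is an estimate reported as adjusted that equals the unadjusted one.

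**Working it through.** **Inputs from the protocol article.** Two visits; time, group and time × group fixed; subject random; 160 participants, so 80 per group; 30% attrition; correlation 0.6 between visits. Completers: 80 × 0.7 = 56 per group, 112 in all. The plan gives no figure for confounding, so there is none to reproduce. Imbalance sizes and confounder strengths below are assumptions.

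**1. Does a main-effect covariate move the estimate?** Write the two responses of subject i, in group g, with baseline covariate x, as

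- y0 = a + b·g + c·x + u + e0
- y1 = a + b·g + d + θ·g + c·x + u + e1

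Subtracting gives y1 − y0 = d + θ·g + (e1 − e0). The term c·x cancels, as does any subject, group or pair intercept. With complete pairs the estimate of θ is the difference in mean change, with or without x. If instead change depends on x with slope γ, and the groups differ by δ in x, the estimate is biased by γδ whether or not x is a main effect. Only x × time removes it.

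**2. Simulation check.** True effect 0, 80 per group, averages over 150 data sets (first row) or 60 (other rows), in units of the outcome's residual SD:

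| Scenario | No covariate | Covariate as main effect | Appropriate term |
|---|---|---|---|
| Confounder of change differs by 0.5 SD, complete data | 0.212 | 0.212 | 0.013 (confounder × time) |
| Same, about 30% dropout | 0.166 | 0.173 | −0.018 (confounder × time) |
| Baseline outcome differs by 0.5 and change depends on it, complete data | −0.195 | −0.195 | 0.001 (ANCOVA of the 12-month value on baseline) |
| Confounder with constant effect over time, complete data | −0.002 | −0.002 | none needed |

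In the first row the largest difference between the two models in any data set was 5 × 10⁻¹⁵. The third row agrees with the regression-to-the-mean formula −(1 − r)·δ = −(1 − 0.6) × 0.5 = −0.20. In that row confounder × time does not help (−0.194); only conditioning on the baseline outcome does. In the fourth row ANCOVA on the baseline outcome alone introduces 0.064, against 0.004 with the confounder added. Neither analysis is safe in every case.

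**3. Baseline outcome as covariate.** Take unit variances and correlation r. The slope on y0 is 1 at baseline and r at 12 months, so the pooled slope is (1 + r)/2. Residual variances are (1 − r)²/4 at baseline and (1 − r)(5 + 3r)/4 at 12 months, with mean (1 − r)(3 + r)/4. The covariance of the two residuals is −(1 − r)²/4, which is negative, so a subject variance bounded at zero is estimated as zero.

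- Model-based variance of θ with n per group: (4/n)·(1 − r)(3 + r)/4 = (1 − r)(3 + r)/n
- True variance: 2 × 2(1 − r)/n = 4(1 − r)/n
- Ratio of standard errors: √((3 + r)/4) = √(3.6/4) = 0.949 at r = 0.6

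The nominal 5% test then rejects with probability P(|Z| > 1.96 × 0.949) = P(|Z| > 1.86) = 6.3%.

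**4. The trigger.** If imbalance meant p < 0.05 in a two-sided test with 80 per group, the noncentrality is δ·√(80/2). For δ = 0.3 this is 0.3 × 6.32 = 1.90, and the power is 47%. For 0.2 SD it is 24%, and for 0.5 SD 88%.

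**5. The texts side by side.** The analysis section adjusts only if imbalance occurs; the Discussion says measured confounders are controlled. Frequency matching aligns group distributions; pairwise matching forms pairs. Each pair of statements needs reconciling.

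**The case against.** The strongest reply is that the text never says the covariates enter as main effects only. It speaks of covariates within appropriate mixed models, and a condensed article may leave their form to a fuller plan. That stands as a limit: the main-effect reading is the plain one, but it is inferred. The authors may have meant an ANCOVA of the 12-month value on baseline. Then the baseline outcome would adjust, but time and time × group could not stay in the model as written, so the section would still need correcting.

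A reader might infer that the plan controls no confounding. The documents do not support that. Time × group removes additive confounding that is constant over time, measured or not, and four sociodemographic factors are matched by design. What remains is confounding of change, and regression to the mean. No figure in the article shows how large either is.

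A reader might also infer that the inflated type I error applies throughout. It applies only if the baseline value is the outcome itself, and at the plan's own correlation it is small. Likewise, the article plans baseline tests but does not say that p < 0.05 defines imbalance, so the 47% is conditional.

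These replies narrow the point. They do not rescue the sentence: it states a remedy that, as worded, does not reach the effect estimate.

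**Conclusion.** Wrong as written. On the plain reading, the conditional covariate leaves the time-by-group estimate unchanged with complete pairs (exact algebra) and nearly unchanged with 30% dropout (0.166 against 0.173 in the simulated case). It therefore does not address confounding of change or regression to the mean. If the covariate is the baseline outcome, the standard error is about 5% too small at r = 0.6 and type I error is about 6.3%, assuming a random intercept with its variance bounded at zero. Making adjustment depend on an observed imbalance does not suit non-randomised groups and contradicts the Discussion.

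The sizes of bias are illustrations under assumed imbalances and confounder strengths, not estimates for this study. The mismatch between frequency and pairwise matching is a separate inconsistency in wording and adds nothing to the algebra.

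**What to change.** Replace the conditional sentence with, for example:

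> Whatever the baseline comparisons show, all models include the pre-named sociodemographic confounders (the matching factors age range, gender, household income and household composition, plus education), each with its interaction with time. The t0 outcome is kept as a response and is not also entered as a covariate. An ANCOVA of t1 on t0 plus these covariates is a sensitivity analysis.

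With complete pairs the main model is equivalent to regressing change on group plus these covariates. The ANCOVA is needed because covariate × time terms do not deal with regression to the mean.

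Keep gardening experience and calendar month out of the main model, as sensitivity analyses at most, because overlap is limited by design. Controls must have no community or home gardening experience, whereas new gardeners are excluded only for community gardening in the household. Gardeners are recruited from March to November and the control survey runs from May to December, so March and April have no controls. With follow-up exactly 12 months later, stable seasonality already cancels within subject.

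Name one matching method in both places. A pair intercept is not a remedy, since it too is constant over time.

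Cost: analysis wording only, as the sociodemographic variables are already collected. The added terms use degrees of freedom on about 112 completers. If the five factors took one to three contrasts each (an assumption), that is 5 to 15 of the 112 − 2 = 110 residual degrees of freedom in the change regression.

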## Discussion

There is growing interest in urban gardens as a way to address environmental and health issues of urbanization [8]. The JArDinS study will lend insight into the effectiveness of community gardens as a tool for promoting sustainable health strategies in a European context. In the field of public health, strategies that promote a sustainable lifestyles are needed to respond to current and future problems and challenges. We will therefore go beyond the health components of the lifestyles and add environmental and economic considerations. For the health dimension, we argue that after 1 year, the experience of the community garden should lead to a heathier food supply, increased physical activity and a feeling of more mental well-being and less social isolation. For the environmental dimension, we will examine to what extent the environmental awareness generated by the experience of the community garden can foster a closer connection with nature, more sustainable food supply strategies and greater sensitivity to food waste. For the economic dimension, we will determine whether the improvement in the healthiness of food supply impacts the level of household food expenditure after 1 year of community gardening. The components of the lifestyles will be compared with one another to help gain an overall understanding of the lifestyles. In particular, the compatibility between the three dimensions of sustainability will be explored for the food supply by looking at the relationships between nutritional quality indicators, cost and the environmental impact of household food supply, together with the carbon impact of trips made for food purchases.

A major strength of this study is its longitudinal design with the use of pretest and posttest assignment and a control group that will explore the causality inference. Another strength is the objective measurement of food supply practices and physical activity using the food supply diary and the Actigraph. Compared to self-report methods, objective measurement tools are insensitive to recall and response bias and so provide more relevant and reliable information [46–49]. In earlier literature, the relation between gardening and nutrition was mostly assessed through declared F&V intake [10–13]. At the interface between food environment and food consumption, food supply has the advantage of providing unique in-depth information on food sources and food items along with accurate up-to-date information on expenditures and quantities purchased [50, 51]. Similarly, accelerometers have gained considerable popularity in recent years as an accurate tool to measure energy expenditure and estimate physical activity. Accelerometers are convenient and non-invasive and can be used relatively easily in free-living conditions to capture large amounts of data over several days [49]. Besides, the automatic activity-recognition model used in the study to derive information on physical activity from raw triaxial accelerometry data was found to improve physical activity energy expenditure and total energy expenditure predictions from a hip-worn triaxial-accelerometer in free-living conditions, compared with traditional count-based prediction approaches [33].

The study has some limitations. First, although several well-known confounders will be measured in the study and controlled in the analyses, the use of a natural experiment makes it difficult to control all extraneous variables, and so unknown and unmeasured extraneous variables may affect the results, threatening validity. Second, the natural experiment and control groups might differ in some pre-study characteristics because participants are not assigned randomly to the two groups, which is liable to bias the estimates of the experiment. Non-random design can threaten the internal validity of the study, which is critical for determining a causal relationship [25]. To ensure similarity between groups, the members of the control group will be selected using pairwise matching on sociodemographic characteristics known to be associated with the outcomes of interest. Third, we will collect frequency and type of foods consumed away from home, but this information lacks precision regarding the quantity consumed and the price paid for food out of home. Nonetheless, studies have shown that nutrients derived from foods purchased at supermarkets provide a good estimate of dietary intake [51–53]. In addition, in France, most meals are still consumed at home [54] and so we expect food supply to be a good proxy of food intake. Fourth, the economic dimension of sustainability will be assessed only by the cost of the diet: other aspects such as ethical consideration (e.g., economic fairness including fair remuneration for producers) [55] will not be investigated.

Public policies are now emerging in France to promote good health and sustainable development of cities. For instance, community gardening undertaken jointly with other food initiatives (at local and national levels) such as Community Supported Agriculture, or projects at canteens could favour access for all to healthy, good quality local products and thus contribute to more sustainable food systems. The JArDinS study based on a natural experiment will yield findings to guide public and private policies for the organization, physical planning and assignment of urban areas. If the study finds evidence for potential benefits of community gardens to attract individuals to more sustainable lifestyles, then access to a community garden, as way to help promote health and wellness, needs to be facilitated.

## Abbreviations

F&V: Fruit and vegetables
GHGE: Greenhouse gas emissions
MAR: Mean adequacy ratio
MER: Mean excess ratio
PA: Physical activity
RPAQ: Recent physical activity questionnaire RPAQ
WEMWBS: Warwick-Edinburgh Mental Well-Being Scale
WHO: World Health Organization
wk.: Week
